## Abstract

**Background:**

Cognitive impairment is prevalent across neuropsychiatric disorders but there is a lack of treatment strategies with robust, enduring effects. Emerging evidence indicates that altitude-like hypoxia cognition training may induce long-lasting neuroplasticity and improve cognition. We will investigate whether repeated cognition training under normobaric hypoxia can improve cognitive functions in healthy individuals and patients with affective disorders and the neurobiological underpinnings of such effects.

**Methods:**

In sub-study 1, 120 healthy participants are randomized to one of four treatment arms in a double-blind manner, allowing for examination of separate and combined effects of three-week repeated moderate hypoxia and cognitive training, respectively. In sub-study 2, 60 remitted patients with major depressive disorder or bipolar disorder are randomized to hypoxia with cognition training or treatment as usual. Assessments of cognition, psychosocial functioning, and quality of life are performed at baseline, end-of-treatment, and at 1-month follow-up. Functional magnetic resonance imaging (fMRI) scans are conducted at baseline and 1-month follow-up, and [^11^C]UCB-J positron emission tomography (PET) scans are performed at end-of-treatment to quantify the synaptic vesicle glycoprotein 2A (SV2A). The primary outcome is a cognitive composite score of attention, verbal memory, and executive functions. Statistical power of ≥ 80% is reached to detect a clinically relevant between-group difference with minimum *n* = 26 per treatment arm. Behavioral data are analyzed with an intention-to-treat approach using mixed models. fMRI data is analyzed with the FMRIB Software Library, while PET data is quantified using the simplified reference tissue model (SRTM) with centrum semiovale as reference region.

**Discussion:**

The results will provide novel insights into whether repeated hypoxia cognition training increases cognition and brain plasticity, which can aid future treatment development strategies.

**Trial registration:**

ClinicalTrials.gov, NCT06121206. Registered on 31 October 2023.

**Supplementary Information:**

The online version contains supplementary material available at 10.1186/s13063-024-08463-5.

## Background

Cognitive impairment across memory, attention, and executive functions is a core dimension of several neuropsychiatric disorders that persists after remission, hampers recovery, and contributes to socio-occupational disability [1–3], which is the largest socio-economic burden of the disorders [4]. This highlights cognitive impairment as a pressing treatment target to improve the lives of patients and reduce societal costs. However, there are no approved treatments with efficacy on cognition in affective disorders, including bipolar disorder (BD) and major depressive disorder (MDD) [5, 6], or in schizophrenia [7]. Cognitive remediation interventions produce overall small to moderate cognitive benefits according to recent meta-analyses in affective disorders [8] and schizophrenia [9], but a large proportion of patients show no improvement [10]. A breakthrough in treatment strategies seems only possible if we move beyond the current understanding of brain processes involved in cognitive health and disease.

Neuroplasticity is the ability of the brain to adjust to challenges by forming new synapses, dendritic spines, and connections and modifying circuit wiring. It is of fundamental importance for cognitive functions and its aberration is involved in cognitive impairments across neuropsychiatric disorders [11]. Many studies have investigated pharmacological treatments acting on pathways involved in neuroplasticity but show only preliminary results [5–7, 11]. Recently, “plasticity-based” computerized cognitive training was found to increase markers of neuroplasticity [12] and cognition in schizophrenia [13], albeit with mixed results [13, 14]. A key challenge that impedes discovery of cognition treatments with robust and long-lasting efficacy is the incomplete understanding of mechanisms underlying *enduring* neuroplasticity.

The fundamental importance of oxygen for animal life has been understood for centuries. William G. Kaelin Jr., Sir Peter J. Ratcliffe, and Gregg L. Semenza obtained in 2019 the Nobel Prize for their discovery of hypoxia-inducible factors (HIF), key transcription factors that regulate gene expression in response to decreases in cellular oxygen availability. Among the HIF regulated genes is erythropoietin (EPO), encoding a potent (hematopoietic) growth factor and, consequently, leading to increased red blood cell production. However, little is known about how oxygen manipulation influences brain plasticity and cognitive functions. In contrast with the lay view that low ambient oxygen has only adverse effects on the central nervous system, *compiling evidence indicates otherwise*. Exposure of neural progenitor cells to low oxygen increases their numbers, survival, and maturation [15]. Imitating hypoxia by stabilizing HIF also improves cognition in healthy mice [16]. Intermittent *moderate* reduction in ambient oxygen (O_2_) from 21% (sea-level) to 9–16% (corresponding to the partial pressure at ≈ 2100–6700 m altitude) enhances the recovery of limb function and respiration after spinal cord injury in animals and humans, effects that are augmented by task-specific training [17, 18]. In a recent systematic review, we examined the evidence for benefits of moderate hypoxia interventions on cognition, neurological functioning, and markers of neuroplasticity across 8 human and 48 animal studies [19]. A key finding was that repeated exposure to lower doses of moderate hypoxia (10–16% O_2_) for 30–240 min over several weeks, ideally in conjunction with physical exercise or motor-cognitive training, yielded neuroprotective effects and potential cognitive benefits. However, larger and methodologically robust translational studies are needed to further validate these findings [19, 20].

Erythropoietin (EPO) is a protein that, in addition to its effects on red blood cell production, plays a fundamental, evolutionarily ancient role in neurodevelopment, neuroprotection, and cognition. EPO and its receptor (EPOR) are present also in insects where they facilitate neuroprotection [21, 22]. In mammals, EPO and EPOR are expressed in hippocampus and cortex and are upregulated upon brain injury or hypoxia [23], which is an endogenous neuroprotective mechanism [23]. Systemically injected EPO crosses the intact blood-brain barrier also in humans and has neuroprotective and neurotrophic effects [23–25]. We found some evidence that EPO can improve cognition in healthy participants and patients with MDD, BD [26–33], schizophrenia, or multiple sclerosis [34, 35], and that this was accompanied by reversal of hippocampal volume loss [28, 31, 33] and enhanced task-related frontoparietal activity [30, 32]. Nevertheless, a major challenge is the cost of EPO and lack of support for clinical trials by EPO producing companies. Thus, alternative ways to increase brain EPO may instead represent a therapeutic breakthrough. We recently discovered that three-week constant moderate hypoxia (12%) combined with motor-cognitive training increases learning capacity and neuroplasticity in mice by inducing mild neuronal hypoxia and upregulation of brain EPO and EPOR [36]. We suggest that this is a key mechanism of long-lasting neuroplasticity and cognitive improvement. While this is an important lead, the discovery of therapeutic effects in animal models provides insufficient prediction of efficacy in humans [11]. A crucial next step is thus to test the efficacy in multidisciplinary human intervention studies.

## Aims and hypotheses

In the ALTIBRAIN project, we will conduct two parallel randomized controlled studies in patients with affective disorders who exhibit cognitive impairments and in healthy participants. Specifically, we will investigate whether three weeks repeated altitude-like hypoxia cognition training (low ambient oxygen and cognitive training) leads to increase in cognitive performance, brain function, and neuroplasticity, effects similar to those seen with intravenous EPO treatment [28, 31, 33–35, 37]. Based on our preclinical studies [36, 38], we expect a long-lasting cognitive improvement accompanied by increase in hippocampal volume and function and in presynaptic density in the hippocampus and prefrontal cortex. Specifically, the ALTIBRAIN trial will test the following hypotheses in healthy participants and in patients with MDD or BD: (i) altitude-like hypoxia cognition training will induce robust cognitive improvement (primary outcome); (ii) this effect will be accompanied by increases in presynaptic density and in regional brain volume and activity measured with positron emission tomography (PET) SV2A [^11^C]UCB-J binding and magnetic resonance imaging (MRI), respectively; (iii) hypoxia with no training and normoxia with training will each induce small transient cognitive increase.

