**Fig. 1 Fig1:**
[figure not shown]
Overview of events across parallel sub-studies

Sub-study 1 involves four intervention groups: (1) normobaric hypoxia (12% O_2_) combined with cognitive training, (2) hypoxia (12% O_2_) with no training, (3) cognitive training under normoxia (20% O_2_), and (4) normoxia (20%) with no training in a double-blinded controlled design. This design enables us to disentangle combined and separate effects of altitude-like hypoxia and cognitive training. Participants are randomized in blocks and undergo interventions in these groups for practical reasons. During the three-week treatment, participants breathe 12% ambient oxygen (≈ 4400 m altitude) or approximately normal sea-level oxygen (20%) in a treatment room, 3.5 h daily, six days per week (18 sessions in total). After a blood test (days 1, 6, 20) and light standardized breakfast, they enter the treatment room. Here, they sit at a desk separated by desk dividers. On iPads, they perform cognitive training or matched control games without cognitive benefits. Cognitive training is interleaved by short breaks, during which the participants can relax or walk on a treadmill inside the room. This is to avoid complete physical inactivity throughout the 3.5 h sessions and thereby make the sessions more pleasant for participants. Participants undergo cognition assessments in weeks 1 (baseline), 4, and 8 and functional and structural MRI in weeks 1 and 8, when red blood cell counts are comparable between groups. Participants in the two extreme groups (normobaric hypoxia with cognitive training and normoxia with no training) will also undergo PET scanning in week 4 (post-treatment). Participants will be recruited consecutively for the PET scans until an equal distribution in each of the extreme intervention arms (i.e., hypoxia with cognitive training and normoxia with no training), sex, and age group is achieved.

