Sub-study 2 involves two intervention groups: (1) normobaric hypoxia (12%) combined with cognitive training 3.5 h daily, five to six days per week for three weeks (16 sessions in total), and (2) treatment as usual (TAU) in an assessor-blind controlled design. Patients in the TAU group will initially be assessed at the same time points as the active group with neurocognitive testing at baseline, week 4, and week 8, fMRI at baseline and week 8, and PET in week 4. After completed testing at week 8, patients in the TAU group undergo the three-week active intervention, followed by one additional neurocognitive assessment and mood rating in the week after treatment completion. The inclusion of this TAU arm rather than an active control group was chosen to ensure patient motivation and minimize attrition in this time-intensive study. Similar study designs with TAU control groups are common in pro-cognitive intervention studies investigating novel treatments in mood disorders and schizophrenia [39, 40]. Although patients will not be blinded to their allocated treatment arm, neurocognitive test results are generally not susceptible to placebo effects [41, 42] and assessments will be carried out by blinded, fully trained research assistants (psychology students).

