**Neuroimaging**						
sMRI + fMRI		x			x	
PET (a subgroup of the participants)				x		

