### Sample size and power calculation

Power calculations were performed with the software program G*Power 3.1.9.4 [74] and were based on the primary hypothesis that altitude-like hypoxia combined with cognitive training produces robust sustained cognitive improvement compared with normoxia and no training (hypothesis i). As hypoxia triggers the endogenous production of EPO, we based the power calculation on our previous clinical study of subcutaneous EPO treatment in which we demonstrated clinically relevant cognitive enhancement [75]. In that study, the differential change between EPO and placebo groups in the same cognitive composite score as we apply in the present study was 0.5 standard deviations (SD) [75]. Assuming an effect of 0.4 SD differential change (medium effect size) between the two groups and 0.5 SD of the change, we will achieve > 80% power to detect an effect at an alpha level of 0.05 by including 26 participants per group. This number of participants provides adequate power for the structural and functional MRI investigations based on our previous studies of EPO [30, 32, 33]. To accommodate for up to a 20% drop-out, we will include 30 participants per treatment arm; i.e., 120 participants in sub-study 1 and 60 patients in sub-study 2.

For PET imaging of SV2A [^11^C]UCB-J binding (reflecting presynaptic density), power calculations involved the following assumptions: (i) the average (SD) *BP*_ND_ in the frontal cortex in healthy participants is 3.36 (0.38) (based on in-house data), and (ii) the combined intervention will lead to a 10% increase in *BP*_ND_. With these assumptions, we will achieve a power of 0.82 to detect an effect at significance level of 0.05 post-treatment of the combined intervention (primary aim) with *n* = 20 per treatment arm using a two-tailed, independent-sample *t*-test.

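### The single week-4 PET scan in two arms supports a between-arm difference for the combined package only; hypothesis (ii) and the mechanism statements should say so, and the PET comparison should adjust for age and sex

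*Protocol article*

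**What the plan says.** Under Aims and hypotheses, hypothesis (ii) concerns the combined hypoxia cognition training and predicts that "this effect will be accompanied by increases in presynaptic density and in regional brain volume and activity", with presynaptic density read from SV2A binding on PET.

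Study design and procedure sets the PET schedule. In sub-study 1, participants in the two extreme groups "will also undergo PET scanning in week 4 (post-treatment"). The subset is filled by quota: "Participants will be recruited consecutively for the PET scans until an equal distribution in each of the extreme intervention arms", and likewise for sex and age group. In sub-study 2 the schedule is "fMRI at baseline and week 8, and PET in week 4". Table 1 agrees. Its row "PET (a subgroup of the participants") has a single mark, at end of treatment, whereas MRI is marked at baseline and week 8.

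The same section says that sub-study 1 will establish causal mechanisms of change in neuroplasticity, and that its four arms allow the separate and combined effects of hypoxia and training to be told apart. The Strengths section repeats this and names PET presynaptic density among the levels of evidence. None of these statements excepts PET.

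Sample size and power calculation takes a mean (SD) binding potential "in the frontal cortex in healthy participants is 3.36 (0.38) (based on in-house data") and assumes that "the combined intervention will lead to a 10% increase in" binding. With 20 per arm and a two-sided independent-sample t-test, it claims a power of 0.82 "to detect an effect at significance level of 0.05 post-treatment of the combined intervention (primary aim").

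**The concern.** One sentence predicts increases in three quantities. Two of them, volume and activity, have a baseline. The third, presynaptic density, has none, so no individual change in binding can be calculated. A reader of the results could take a week-4 difference between arms as observed growth within people.

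In sub-study 1 the two scanned arms differ in both oxygen level and training. A PET difference between them could come from hypoxia, from training or from the two acting together, and the PET data cannot say which. The four-arm design answers that question for cognition and MRI but not for PET. The general statements would let a package effect on binding be reported as if its cause had been identified.

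The stated PET test also leaves out factors that the design itself uses. Age is a randomisation stratum (Randomization and blinding), and sex and age group are quota variables for the PET subset. If either is related to binding, a plain t-test keeps in its error term variation that the balancing has largely removed from the arm comparison. It is then less precise than it need be.

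**Working it through.** **1. The plan's own figure.** Inputs from Sample size and power calculation: mean 3.36, SD 0.38, effect 10%, n = 20 per arm, two-sided alpha 0.05.

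- Difference: 0.10 × 3.36 = 0.336.
- Standardised difference: 0.336 / 0.38 = 0.884.
- Standard error: 0.38 × √(2/20) = 0.120.
- Noncentrality: 0.336 / 0.120 = 2.80 on 38 degrees of freedom.
- Exact power: 0.778 (normal approximation 0.798).

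The stated 0.82 is not reproduced. A one-sided test gives 0.865, and rounding the standardised difference to 0.90 gives 0.792. About 22 per arm would be needed (0.817). This is a side observation, but it shows that the PET comparison has no precision to spare.

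**2. What each measure can estimate.**

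| Measure | Time points | Arms scanned, sub-study 1 | Within-person change | Hypoxia and training separable |
|---|---|---|---|---|
| MRI volume and activity | Baseline, week 8 | All four | Yes | Yes |
| PET binding | Week 4 | Two extreme arms | No | No |

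With arm means written as HT (hypoxia, training), H (hypoxia only), T (training only) and C (neither), the PET contrast is HT − C = (H − C) + (T − C) + interaction. One observed difference cannot determine three terms. Sub-study 2 compares the combination with treatment as usual, so the same limit applies there.

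**3. What the missing baseline costs.** Allocation is random, so the week-4 comparison is valid without a baseline. Simulating two equal arms of 20 gave a type I error of 0.053, close to nominal. The loss is precision. The correlation r between baseline and week-4 binding is not in the article. If a baseline scan existed and r were 0.5 or 0.7, a baseline-adjusted analysis with the same 20 per arm would have power 0.88 or 0.97.

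**4. What age and sex adjustment could bring.** If age and sex explain a share R² of the variance in binding, the residual SD is 0.38 × √(1 − R²), and two covariates reduce the degrees of freedom from 38 to 36. R² is not in the article, so it is assumed over a range:

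| Assumed R² | Residual SD | Power, n = 20 per arm |
|---|---|---|
| 0 | 0.380 | 0.777 |
| 0.05 | 0.370 | 0.797 |
| 0.10 | 0.360 | 0.818 |
| 0.20 | 0.340 | 0.860 |

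If the covariates explain nothing, the loss is about 0.001 in power (0.778 to 0.777). These figures treat age and sex as balanced between the arms, as the quota intends.

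**The case against.** The strongest reply is that hypothesis (ii) never says within-person. The power section makes it operational as a post-treatment comparison of the combined intervention with control, and there an increase can only mean relative to control. Hypothesis (ii) also does not promise to separate the components. Hypothesis (iii) does, and it concerns cognition. The restriction to two arms is stated openly, and a single scan is an understandable choice for a radioactive tracer in a proof-of-concept study. All of this stands. It shows that the PET test is sound for what it tests. It does not remove the general statements in Study design and procedure and in Strengths, which claim more for PET than that test can give.

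A second reply is that a t-test named in a power calculation does not fix the analysis, and that the covariates may be settled in a fuller plan. That is fair. The Positron emission tomography analyses section names no model for comparing groups, so the t-test is simply the only comparison the article states. Adjustment is therefore put forward as an improvement that matches the design and not as the repair of an invalid test.

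A reader might go further and infer that chance imbalance in unmeasured baseline binding undermines the comparison. The between-person SD is 0.38 / 3.36 = 11.3% of the mean against an expected 10%, and one standard error is 0.120 / 0.336 = 36% of the expected effect. But that standard error is the quantity the t-test already divides by, so chance imbalance is covered by the alpha level. A reader might also suspect that selection for PET depends on arm. The subset is filled with arm as a quota variable, but the listed PET exclusions are not arm-specific and nothing in the article shows such dependence.

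**Conclusion.** The point holds as a limit on what PET can conclude, together with a low-cost improvement to its analysis. At week 4 the trial can estimate the difference in binding attributable to the combined package, provided that inclusion in the PET subset does not depend on arm. It cannot measure an individual increase, and it cannot divide the effect between hypoxia and training. The causal-mechanism and separate-effects statements are too broad for PET by that much.

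The documents do not support the stronger reading that PET cannot show any increase. Because the arms are randomised, higher binding than control is evidence of an effect of the package. Nor do they support a criticism of relating binding to cognitive change, since no such analysis is planned; the only correlation with cognitive improvement that is described concerns blood biomarkers.

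The size of the analytic gain rests on an assumed R²: power moves from 0.778 to between 0.777 and 0.860 for R² from 0 to 0.20. The primary cognitive outcome is not affected.

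**What to change.** 1. Word the PET part of hypothesis (ii) as higher regional binding potential at week 4 in the hypoxia-plus-training arm than in the control arm. Keep the language of change for MRI, which has a baseline.
2. State that the PET contrast concerns the combined intervention only, in both sub-studies. Except PET from the separate-effects statement in Study design and procedure, and from the causal-mechanism statements there and in Strengths.
3. Analyse week-4 binding with a linear model on arm, adjusting for age (or age group) and sex, and specify this before the PET data are analysed by arm.

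All of this uses data already collected and needs no further scans. The cost is a narrower mechanistic claim and about two degrees of freedom.

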## Methods

### Study design and procedure

In a basic scientific study in healthy humans, we will determine the causal mechanisms of changes in neuroplasticity and cognition across multiple levels of analysis (sub-study 1). The clinical study (sub-study 2) will in parallel clarify whether targeting these mechanisms translates into cognitive benefits in cognitively impaired patients, in line with a phase II study design. In this way, both studies will provide proof-of-concept evidence for potential benefits of intermittent hypoxia combined with cognitive training on brain plasticity and cognitive functioning*.* Figure 1 depicts an overview of study events.

